| Introduction | Annually, colorectal cancer affects approximately 1.25  million people worldwide. (1) Despite the undeniable  advances in early disease screening and curative  management, about 50% of patients have metastatic disease,  either at diagnosis or in its evolution, an incurable and fatal  condition in most cases. (1) As a result, 600,000 people die  each year despite therapeutic advances. Thus, it is essential  to increase and improve the therapeutic range of metastatic  colorectal cancer (mCRC) in order to provide better care for  this huge number of people. In Brazil, consolidated data show  that colon and rectal cancer is the third most common cancer,  being diagnosed in about 30,000 people a year.  Since the estimated number of individuals with type 2  diabetes taking metformin daily is over 100 million,  epidemiologists have examined the effect of metformin on  cancer incidence. Initial results showed a reduction in the  amount of cancer in individuals taking metformin compared to  any other drug. Similarly, a recent breast cancer study in  patients with type 2 diabetes who were taking metformin  showed a significant increase in pathological complete  response, and a large phase III study to evaluate metformin  as adjunctive treatment is under development.  The mechanism by which metformin exerts its effects  on antineoplastic therapy is unclear, however AMPK inhibition  of the mTOR pathway is one of the main mechanisms pointed  out.  Preclinical data from our laboratory showed synergistic  antitumor effect of irinotecan combined with metformin on  growth of graft colon cancer lineage in immunodeficient mice (SCID mice) following treatment of mice with irinotecan and rapamycin at doses that reduce tumor growth “in vivo” for each agent alone. Although tumor growth has been reduced in mice treated with each agent alone, the tumors still increased approximately fivefold. In contrast, tumor growth in animals treated with the combined drugs was completely blocked.  These data demonstrate that the combined use of AMPK  activator with irinotecan dramatically reduces tumor growth  “in vivo”.  Metformin is a recognized AMPK activator. |
| Purpose/ Justification | In this study we are planning to evaluate the safety and efficacy of metformin combined with irinotecan in patients with recurrent or metastatic colon and rectal cancer (mCRC) who have failed all conventional chemotherapy regimens available and are not candidates for surgical treatment with curative intent. These patients do not have valid therapeutic options approved by national regulatory agencies. |
|  | The treatment of cancer represents a public health challenge, so federal expenses are rising. Colorectal cancer appears in this scenario as one of the most incident neoplasms in Brazil and as a disease in which therapeutic alternatives are restricted after their recurrence. On the other hand, currently established therapies are considered fertile soil for the development of modern cancer drugs. The union between the use of drugs already established with a new indication results in less spending both in the experimental stage, not being necessary to establish a toxicity profile, and in the application phase, which can result in reduced costs, since these drugs no longer have patents. |
| Objectives | Primary Objectives: To evaluate the disease control rate at week 12 (after four treatment cycles) and the safety of the combination of metformin and irinotecan in the treatment of patients with refractory mCRC treated with chemotherapeutic drugs available in Brazil for this disease.  Secondary Objectives: To evaluate response duration, objective response, disease progression-free survival (DPS), and overall survival (OS). Still, quality of life will be evaluated (EORTC QLQ-C30 and QLQCR29 questionnaire). |
| Study Design | This is a multicentric, prospective, single arm, phase II, two-stage study to investigate the efficacy and safety of the combination of irinotecan and metformin in patients with metastatic colorectal cancer. If being a promising regimen, there may be a further extension to a phase III study. The primary endpoint is the disease control rate at the 12^th^ week of treatment. |
|  | The primary endpoint is the disease control rate (stable disease + partial response + complete response) at the twelfth week of treatment. The efficacy assessment will be by intention of treatment. The metformin and irinotecan combination will be administered continuously until disease progression by RECIST v1.1 criteria or in case of severe toxicity or withdrawal of consent.  Sample size was calculated according to the optimal design of Simon. Considering a DCR of 13,2% on week 12 with placebo in third line, we believe that it would be clinically significant to increase this DCR to 26,7% .Considering an alpha error of 10% and a beta error of 20%, we planned to enroll 41 patients. This study would be considered positive if at least 9 patients had disease control on week 12.  This is a multi-institutional study, and it will take place at the Clinical Research Unit of Barretos Cancer Hospital.  Metformin will be given at a dose of 1500mg / day orally for 7 days, initially, and escalated to 2500mg / day if tolerated after one week of use, plus irinotecan at a dose of 125 mg per square meter body surface area D1 and D8 every 21 days. All patients will be treated until disease progression or appearance of prohibitive toxic effects. Those with a complete radiological response (CR) may discontinue irinotecan use two cycles after the diagnosis of CR (only if a total of six cycles is reached) at the investigator’s discretion, as well as those without presenting progression after two consecutive response assessments.  Tumor response will be assessed by computerized tomography (CT) or magnetic resonance imaging (MRI) every two cycles in the combined metformin and irinotecan phase and every twelve weeks during the metformin phase alone.  Toxic effects will be analyzed according to the National Cancer Institute Common Toxicity Criteria for Adverse Events, version 4 (NCI CTCAE v4). |
| Population | The target population includes adult patients with histologically confirmed or recurrent metastatic RCC refractory to treatment with oxaliplatin, irinotecan, fluoropyrimidine and an anti-EGFr agent if it is wild K-ras. |
| Inclusion/  Exclusion  Criteria | Inclusion Criteria:  Patients aged 18 years and over;  Patients with colon and rectal adenocarcinoma, with  recurrent or metastatic disease, refractory to treatment  based on oxaliplatin, irinotecan, fluoropyrimidine and, in  the case of wild K-ras patients, should also be resistant to  cetuximab or panitumumab;  Evaluable disease according to RECIST 1.1 criteria;  ECOG 0-2;  Suitable hematological functions (hemoglobin ≥ 9.0 g / dL;  neutrophil count ≥ 1,500 / mm3 and platelet count ≥  100,000 / mm3), adequate renal function (serum creatinine  less than 1.5 times the normal upper limit) and adequate  liver function (bilirubin less than 1.5 times the normal limit;  aspartate aminotransferase and alanine aminotransferase  less than five times the normal limit when there is liver  metastasis, or 2.5 times the normal limit, when the liver is  free of secondary lesions);  Exclusion Criteria:  Patients with known hypersensitivity to and/or prior to  irinotecan and metformin therapy;  Chronic treatment with immunosuppressive agent or  corticosteroids at a dose greater than 10 mg/day of  prednisone ;  Patients with known central nervous system (CNS)  metastases;  Patients with a previous diagnosis of another neoplasm,  except for basal cell carcinoma of the skin and noninvasive  cervical cancer;  Known HIV-positive patients will be accepted provided they do not have active AIDS-defining illness or AIDS- associated condition that compromises the safety of patients with stable antiretroviral treatment and reconstituted immunity (CD4 lymphocyte count ≥200/mm³, regardless of viral load);  Chronic or acute active infection (except known HIV  infection with no relevant immune repercussions);  Patients with active bleeding or hemorrhagic diathesis;  Patients with any uncontrolled serious medical condition or  other conditions that may affect their participation in the  study;  Patients who are taking another study medication or who  have received study drugs for less than 4 weeks;  Patients who are pregnant or nursing;  Diabetic patients on metformin treatment;  Absolute contraindication to loperamide use. |

| Dose, treatment cycle | Metformin will be given at a dose of 1500mg/day (two pills in the morning at breakfast and one at dinner) for seven days. If there is no prohibitive adverse effect at 1500mg/day, the dose will be increased to 2500mg/day (three pills in the morning at breakfast and two at dinner), and this dose will be maintained until PD or unacceptable toxicity. Metformin will not be administered within two days prior to contrast infusion examinations at the discretion of the radiologist to minimize the risks of lactic acidosis.  Irinotecan will be administered at a dose of 125 mg/m² intravenously D1 and D8 every 21 days. |
| --- | --- |
| Preparation and administration | Metformin will have 500mg presentation. Not dosed by weight or body surface area. Irinotecan will be diluted in 5% dextrose solution. Its infusion will be performed intravenously, lasting 90 minutes. The irinotecan infusion will be preceded by the infusion of dexamethasone 20mg and ondansetrone 16mg. |
| Schedule of visits and evaluations | Study evaluations will be performed at the screening period (D-21 to D-1), the day of study initiation (D1), at D8 of the first cycle and at D1 of the subsequent cycles. |
| Effectiveness Assessments | Tumor assessment (CT or thoracic MRI, abdominal and pelvic) will be performed every 6 weeks until the 12^th^ week of initiation of treatment and after 12 weeks or at any time during the study where clinical progression is suspected. Any suspicion of progression due to clinical deterioration should be accompanied by radiological confirmation.  All images will be analyzed locally at the centers and this interpretation will be used for all clinical decisions. RECIST criteria will be used for primary endpoint analysis. |

1. Introduction

1.1 Colorectal cancer

  Annually, colorectal cancer affects approximately 1.25 million people worldwide. (1) In Brazil, consolidated data show that colon and rectal cancer is the third most common cancer, being diagnosed in about 30,000 people a year.

The importance of this disease is felt in the volume of studies that investigate its biology. Many of these studies had direct repercussions on their management. The oncogenesis of this disease is quite well described, which allowed the elaboration of effective strategies for screening the premalignant component and early disease, with direct repercussions on survival. (2-6)

Refinements of local care, through isolated surgery or combination of radiotherapy and surgery have improved local control of the disease. (7-9) Pre- and postoperative (neo- or adjuvant) chemotherapy has been used since the eighties, improving cure rates consistently. (10, 11) Despite undeniable breakthroughs in early disease screening and curative management, about 50% of patients present metastatic disease, either at diagnosis or disease progression, incurable condition and fatal in most cases. (1) Thus, 600,000 people die each year despite therapeutic advances. Therefore, it is essential to increase and improve the therapeutic range of metastatic colorectal cancer (mCRC) in order to provide better care for this great amount of people.

Even considering that only a few patients with metastatic disease achieve cure, there have been significant improvements in palliative mCRC management. Within a short period of twenty years, the patient with metastatic colorectal cancer (mCRC) who, if left untreated had an average of 6 months overall survival, could view median overall survival reaching 30 months or even a real, however small chance of cure for very selected cases. (12, 13)

These advances in the management of mCRC occurred mainly through the emergence of different lines of chemotherapy treatment. From the isolated use of 5-fluorouracil, fluoropyrimidine, it evolved to its combination with folinic acid, enzymatic cofactor, tactic that increased survival from 9 months to 12 months with significant decreasexin toxicities.(12)

The next step was the emergence of other lines of therapy through the use of new chemotherapeutic drugs such as oxaliplatin and irinotecan. Oxaliplatin is a platinating agent that can directly damage CCR cell DNA with potentiated effect when combined with a fluoropyrimidine. Irinotecan is an inhibitor of topoisomerase I, being able to damage DNA by preventing topological stresses from being corrected and leading to fragmentation of single and double strands of DNA. The combination of these drugs with fluoropyrimidine, as in the Folfox and Folfiri regimens, and the sequential use of these regimens allowed the median overall patient survival to reach nearly two years. (12)

Another milestone in the management of mCRC was the introduction of biological agents such as monoclonal antibodies and anti-EGFR (cetuximab and panitumumab) and anti-VEGF (bevacizumab, aflibercept and regorafenib) tyrosine kinase inhibitors. (13-16) These medications can enhance the efficacy of conventional chemotherapy regimens or increase overall survival when monotherapy. The sequential use of all available weaponry has led us to imagine that mCRC could become a long-term chronic disease or in some cases even curable with associated surgery.

However, initial expectations could not be confirmed. Fewer than 10% of patients with mCRC can be cured by combined surgery and chemotherapy. (17) Anti-EGFR agents have restricted benefit to only 40% of patients whose tumors have the EGFR pathway without mutation in several enzymes, being K-ras the principal one. (18, 19) Even for patients with tumors without activating mutation along the EGFR pathway, the addition of anti-EGFR agents is not able to bring about cure or prolonged disease control. For patients with mutated K-ras tumors, there is no benefit from the use of anti-EGFR agents, and the use of cetuximab is actually deleterious in these patients. (18) Thus, the scenario is much more limited for those patients having tumors with mutation in the EGFR pathway.

There is no biomarker yet that allows choosing patients who benefit from the use of bevacizumab or aflibercept, which prevents the rational use of financial resources to afford very expensive treatment. Even regorafenib, the newest multi-kinase drug against mCRC, lacks biomarker that indicates who should be treated and who may be spared from the side effects of this medication. In fact, all these new medications have their use frankly limited by the cost. (20)

Despite these limitations, studies continue to uncover new strengths and weaknesses of mCRC. One drug that may perform anti-tumor activity is metformin. It is estimated that 100 million people use metformin daily to control type II diabetes. Early epidemiological studies have shown a reduction in the amount of cancer in individuals taking metformin compared to any other drug. (21, 22) Similarly, a recent study of breast cancer in patients with type 2 diabetes who were taking metformin showed a significant increase in pathological complete response (23) and a large phase III study to evaluate metformin as an adjuvant is under development. (24) These studies use the metformin dose commonly used in the clinic for type II diabetes control. , precluding a phase I clinical study. (25) Preliminary data from a randomized study conducted and led by our group comparing paclitaxel with or without metformin as a palliative treatment of cisplatin-refractory head and neck cancer patients has encouraging data (<http://www.saude.sp.gov.br/resources/instituto-desaude/homepage/pdfs/pdfs-em-geral/caderno_of_summary_site_ppsus.pdf> ).

The mechanism by which metformin exerts its effects is unclear; however AMPK inhibition of the mTOR pathway is one of the main mechanisms pointed out. (26) This fact may occur by the phosphorylation of TSC2. (27) And that the TSC1 complex -TSC2 negatively regulates cell growth by acting upstream of mTOR to cause this inhibition. (28) In several solid and hematological tumors, activation of the mTOR pathway plays an important role in tumor biology, conferring greater aggressiveness or refractoriness to anti-neoplastic therapies. Some blockers of this route have been tested in various oncology scenarios with consistent results. The first described inhibitor of mTOR is rapamycin.

Metformin inhibits mitochondrial respiratory chain complex I, resulting in reduced ATP production and consequently AMPK activation (29-32). Thus, activation of this signaling pathway is necessary to reduce circulating glucose levels. (30) However, activation of AMPK not only programs metabolism, but also alters proliferation and cell death suggesting that this drug may be useful in cancer treatment (33)

The insulin signaling pathway is activated when nutrients are available and the AMPK pathway is activated when the cells suffer from the lack of carbon sources. (32) In mammals, insulin promotes the synthesis of lipids, proteins and glycogen and the AMPK inhibits these biosynthetic pathways. The effect of insulin on protein synthesis is mediated in part by activation of the mTOR pathway via TSC2 phosphorylation (Figure1), and the AMPK activation causes TSC2 phosphorylation at sites different from the ones phosphorylated by Akt and inhibits mTOR. (27, 34)

There also seems to be a direct connection between these two ways. In some tissues, such as the cardiac muscle, insulin antagonizes AMPK activation (35, 36) apparently through Akt activation. (37) Apparently this occurs through phosphorylation by Akt serine residues 485 or 491 in the α1 or α2 subunits, respectively, of AMPK, which antagonizes AMPK activation through Thr 172 phosphorylation by LKB1. (38) It is not established yet, whether this mechanism also occurs in other tissues. (32)

[figure not shown]

Figure 1: Interrelation between IRS / PI3 kinase / Akt (PKB) / mTOR pathways and AMPK pathway

Preclinical data from our group showed synergistic antitumor effect of irinotecan combined with an mTOR inhibitor, rapamycin, on the growth of graft colon cancer HT29 strain in immunodeficient mice (SCID mice). (39) As shown in Figure 2, mice treated with irinotecan and rapamycin at doses that reduce tumor growth "in vivo" for each agent alone. Although tumor growth was reduced in mice treated with each agent alone, tumors still increased approximately fivefold. In contrast, tumor growth in animals treated with the combined drugs was completely blocked. These data demonstrate that the combined use of rapamycin with irinotecan dramatically reduces tumor growth “in vivo”.

[figure not shown]

Figure 2. Association of irinotecan and mTOR (rapamycin) inhibitor in preclinical study

1.2 Metformin Overview

Metformin (DCI; marketed as Glifage, Dimefor, Glucoformin, Glucophage, among other brands, and as a generic medicine) is an oral antidiabetic of the biguanide class. The development of the biguanide class was derived from the study of the effects of the plant Galega officinalis, widely used in Europe since the Middle Ages as a popular treatment for diabetes polyuria. (40) Later the chemical compound responsible for the effect was discovered. The plant's hypoglycemic - called galegina - was a guanidine derivative. Guanidine itself is too toxic to use as a medicine, but the development of derivative agents persisted, and in 1957 the first scientific description of metformin was published. (40, 41) Metformin first entered clinical use in France in 1979; in the United States, it was approved only in late 1994, due to longstanding concerns about the safety of biguanides.

### CHEMICAL STRUCTURE

[figure not shown]

[figure not shown]

Figure 3 - Chemical structure of metformin

MECHANISM OF ACTION

  A study published in 2001 showed that metformin stimulates the function of an enzyme called AMPK, which plays an important role in lipid and glucose metabolism, a protein kinase that is capable of inactivating mTOR, a protein involved in growth regulation, proliferation and cell survival.

EXPERIMENTAL ANTI-TUMORAL ACTIVITY

  Metformin has recently demonstrated antiproliferative and proapoptotic effects in different cell lineages, including breast, prostate, and colon cancer. (43-47)

POPULATION STUDIES AND RETROSPECTIVE COHORTS

  Population studies have shown that metformin use decreases the incidence of cancer and cancer-related mortality in diabetic patients. (21, 22) It has recently been observed in a retrospective study that diabetic breast cancer patients receiving metformin and neoadjuvant treatment for breast cancer had a higher response rate than diabetic patients who did not receive metformin. (23)

ADVERSE EFFECTS

Gastrointestinal

The most common adverse effects of metformin are gastrointestinal in nature - nausea, vomiting, diarrhea, gas, cramps and lack of appetite - and are most common at the beginning of treatment or after a dose increase. Metformin seems to cause gastrointestinal discomfort more frequently than most other antidiabetic agents (48). In a US clinical study of 286 patients, more than half of those receiving metformin reported diarrhea, compared with just over 11% of those receiving placebo, and a quarter of patients reported nausea or vomiting, compared with just over 8% of those taking placebo.

Although metformin is well tolerated by most people, its gastrointestinal effects can be quite uncomfortable; it is possible to avoid them by starting treatment at a low dose and gradually increasing it. Abdominal discomfort after chronic (prolonged) use is rare.

Prolonged use of metformin is associated with an increase in blood homocysteine ​​levels (49) and malabsorption of vitamin B12 (50, 51). The higher the metformin dose and duration of use, the higher the incidence of vitamin B12 deficiency; some authors recommend prevention strategies (52).

Lactic Acidosis

The most serious potential adverse effect of metformin is lactic acidosis or lacto acidosis. However, it is quite rare, and seems to occur only in people with impaired liver or kidney function.

Another biguanide, phenformin, has been withdrawn from the market in several countries (including the United States, Portugal and Brazil) due to an unacceptable risk of causing lactic acidosis. Metformin, however, is safer, and it has been shown that it does not increase the incidence of lactic acidosis when known contraindications are observed (53).

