3.3.2. Secondary outcomes

Secondary outcomes include overall response rate (ORR), duration of response, PFS, OS, quality of life, and tolerability. The disease control rate corresponds to the objective response rate plus the rate of stable disease patients.

Progression is defined as an increase of 20% or more in the sum of the largest target lesion diameters, or the appearance of new lesions, according to RECIST v1.1, or death from any cause.

The duration of the response will be measured from the time of CR or PR documentation (whichever is first recorded) to the date of disease progression documentation, with reference to the smallest measures recorded during the course of treatment.

The duration of stable disease will be measured from the moment therapy is started until the criteria for progression are met. The duration of stable disease is conceptually identical to the time to disease progression.

Toxicity will be classified using standard terminology criteria from the American National Cancer Institute for Adverse Events, Version 4. (NCI (73) AE v4). The performance index will be ranked according to the ECOG (US Cooperative Eastern Oncology Group) criteria.

4. Patient Selection Criteria

The target population includes adult patients with histologically confirmed (stage IV or recurrent) mCRC who have failed chemotherapy regimens containing oxaliplatin, irinotecan and fluoropyrimidine and cetuximab or panitumumab if wild Kras, and which have measurable or evaluable disease.

The investigator should ensure that patients meet all inclusion criteria and none of the exclusion criteria to enter the study. In addition, prior to the first dose of study medication, all laboratory biochemistry and hematology values must meet the inclusion criteria.

4.1 Inclusion criteria:

- Patients aged 18 years and over;

- Patients with colonic or rectal adenocarcinoma with recurrent or metastatic disease refractory to oxaliplatin, irinotecan, fluoropyrimidine-based treatment and, if wild Kras, should also be resistant to cetuximab or panitumuabe; We define refractoriness as radiological progression during or within six months of termination of treatment containing all these drugs;

- Not a candidate for any treatment with curative intent, including surgery and radiation therapy;

- Measurable or evaluable disease according to the RECIST 1.1 criteria; (72)

- ECOG 0-2;

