- Appropriate haematological functions (hemoglobin ≥ 10 g / dL [5.6 mmol / L]; neutrophil count ≥ 1,500 / mm3 and platelet count ≥ 100,000 / mm3), adequate renal function (serum creatinine less than 1.5 times the limit). normal liver function) (bilirubin less than 1.5 times the normal limit; aspartate aminotransferase and alanine aminotransferase less than five times the normal limit when there is liver metastasis, or 2.5 times the normal limit when the liver is free of metastasis);

4.2 Exclusion Criteria:

- Patients with known hypersensitivity to and / or prior irinotecan and metformin therapy;

- Chronic treatment with immunosuppressive agent or corticosteroids at a dose greater than 10 mg / day of prednisone;

- Patients with known central nervous system (CNS) metastases;

- Patients with a previous diagnosis of another neoplasm, except for basal cell carcinoma of the skin and noninvasive cervical cancer;

- HIV-positive patients will be accepted if they do not have active AIDS-defining illness or AIDS-associated condition that compromises the safety of patients, with stable antiretroviral treatment and reconstituted immunity (CD4 lymphocyte count ≥200 / mm³, regardless of viral load). ;

- Chronic or acute active infection (except known HIV infection with no relevant immune repercussions);

- Patients with active bleeding or bleeding diathesis;

- Patients with any uncontrolled serious medical condition or other conditions that may affect their participation in the study;

- Patients who are taking another study medication or who have received study drugs for less than 4 weeks;

- Patients who are pregnant or nursing;

- Diabetic patients on metformin treatment;

- Absolute contraindication to loperamide use.

5. Study Design

This is a prospective phase II single arm clinical study designed to evaluate the effect of metformin with irinotecan for patients with progressing mCRC after previous treatment. The primary end point is the disease control rate (stable disease + partial response + complete response) at week 12 of treatment. The efficacy assessment will be by intention to treat. The metformin and irinotecan combination will be administered continuously until disease progression by the RECIST v1.1 criteria or in case of severe toxicity or withdrawal of consent.

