6.1 Administration of medicines

Patients will be asked to take their metformin tablets daily twice a day at approximately the same time each day and should be instructed to swallow the whole tablets with a full glass of water, not chew them. All patients should avoid eating grapefruit during the study as this may increase and prolong exposure to the study drugs.  The vomited, missed or missed doses should not be re-administered and patients should take the next dose on time following the schedule. Interruption of metformin medication for three days prior to infusion of any contrast medium for radiological studies will be allowed at the discretion of the radiology team.

Metformin will initially be administered at a dose of 1500mg / day orally for 7 days, beginning on the first day of chemotherapy infusion. Patients with good tolerance (absence of grade 3 or 4 adverse events) may have metformin dose escalated to 2500 mg / day on the eighth day of the first cycle. This metformin dose and escalation regimen is in line with the current design of metformin research on cancer treatment, either alone or in combination with conventional chemotherapies. (25) These doses are the commonly used and recommended for the treatment of patients with diabetes. type II, whether they have cancer or not.

Patients will receive irinotecan 350 mg / m^2^ intravenously, diluted in 500 mL 5% dextrose solution, in continuous infusion lasting 3 hours on D1 every 3 weeks, exactly as is done in the routine care of this service. ( 75) Prior to irinotecan infusion, the patient will receive the following medications:

1. Dexamethasone 8 mg intravenously 15 minutes before infusion;

2. Ondansetron 8 mg intravenously 15 minutes before infusion;

3. Atropine 0.25 mg subcutaneously.

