6.2 Dose Adjustments

M ETFORMIN

Patients will initially receive 1500 mg / day metformin for 7 consecutive days, and on day 8 they will be clinically evaluated for toxicity. Patients without evidence of serious adverse events (grade 3 or 4) will have metformin dose escalated to 2500 mg / day. In case of intolerance, the dose will be reduced to 1500mg / day. Dose reduction to 1000mg / day will be allowed in cases of grade 3 or 4 toxicity in patients taking metformin 1500mg / day, as well as dose reduction from 2500mg / day to 1500mg / day will also be permitted in cases of intolerance. .

Recovery of acceptable toxicity levels should occur within 3 weeks to allow further study. Those with toxicity that lasts for more than 3 weeks preventing re-introduction of the study drug will be excluded. Reduction of even metformin to level -1 will be allowed (table 1).

Table 1: Available dose levels for metformin.

| Level | Daily dose | Administration |
| --- | --- | --- |
| 1 | 2500 mg / day | 1 x 1500 mg  1 x 1000 mg |
| 0 | 1500 mg / day | 1 x 1000 mg 1 x 500 mg |
| - 1 | 1000 mg / day | 1 x 500 mg  1 x 500 mg |

Doses will be reduced for haematological and other adverse events. Dose adjustments are made according to the system that shows the highest degree of toxicity. Adverse events will be classified using the National Cancer Institute Common Terminology Criteria for Adverse Events Version 4 (NCI CTCAE). (73)

Table 2: Dose modifications for metformin-associated toxicities

| Toxicity | Grade 1 | Grade 2 | Grade 3 | Grade 4 |
| --- | --- | --- | --- | --- |
| Non hematologic | Keep the same  dose level | Maintain the same dose level. The dose may be discontinued until toxicity is ≤ 1 or has returned to baseline at the investigator's discretion. Then resume treatment at the same dose level. | Drop the dose until the toxicity is grade ≤ 1 or has returned to baseline, then resume treatment at the same dose level or reduce the dose to level 1 at the investigator's discretion **. | Drop the dose until the toxicity is grade ≤ 1 or has returned to baseline, then reduce the dose to level -  1 or discontinue treatment at the discretion of the investigator ^#^. |

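### The creatinine and bilirubin limits stop binding at the first dose, so a day-8 value that would have barred entry need not stop the metformin increase to 2500 mg/day if it is below grade 3

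*Protocol*

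**What the plan says.** **Risk.** Section 1.2 (Lactic Acidosis) calls lactic acidosis the most serious potential adverse effect of metformin and says that "it is quite rare, and seems to occur only in people with impaired liver or kidney function". It adds that "it does not increase the incidence of lactic acidosis when known contraindications are observed".

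**Entry.** The synopsis requires creatinine "less than 1.5 times the normal upper limit". Section 4.1 has the same rule, "adequate renal function (serum creatinine less than 1.5 times the limit", and sets bilirubin below 1.5 times the normal limit. Section 4 fixes when these apply: "prior to the first dose of study medication, all laboratory biochemistry and hematology values must meet the inclusion criteria".

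**Escalation on cycle 1 day 8.** The synopsis (Dose, treatment cycle) raises the dose to 2500 mg/day if there is no prohibitive adverse effect at 1500 mg/day. Section 6.1 is permissive: "Patients with good tolerance (absence of grade 3 or 4 adverse events) may have metformin dose escalated to 2500 mg / day". Section 6.2 is directive: "Patients without evidence of serious adverse events (grade 3 or 4) will have metformin dose escalated to 2500 mg / day".

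**Later dose changes.** Section 6.2 adds: "In case of intolerance, the dose will be reduced to 1500mg / day". Table 2 sets the response by grade. Its footnote on starting another cycle names neutrophils, platelets and haemoglobin.

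**Monitoring.** Section 7.2 and Table 3 schedule biochemistry on days 1 and 8 of cycle 1 and on day 1 of each later cycle. Weekly repeat tests for renal or hepatic toxicity begin at grade 3.

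**The concern.** The protocol makes the safety of metformin depend on liver and kidney function and sets numerical limits for both. It then measures the same quantities throughout treatment without tying the same limits to any metformin decision. The sharpest case is day 8: a fresh creatinine and bilirubin are available on the day the dose is due to rise, and a result that would have excluded the patient a week earlier does not stop the increase.

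Safety is part of the primary objective in section 3.1. At stake is avoidable exposure to the harm the protocol itself ranks as most serious. The sample size, error rates and week-12 decision rule are not involved.

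**Working it through.** The plan states no figure to reproduce. The check sets the rules side by side and asks what must happen to metformin when creatinine or bilirubin is above its 4.1 limit.

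**1. Required response by time and grade**

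| Situation | Rule | Required metformin action |
|---|---|---|
| Before first dose, limit exceeded | Sections 4 and 4.1 | Not eligible |
| Day 8, limit exceeded, below grade 3 | Synopsis, 6.1, 6.2 | None; the dose may (6.1) or will (6.2) rise |
| On treatment, grade 1 | Table 2, non-haematological | Keep the dose |
| On treatment, grade 2 | Table 2, non-haematological | Maintain; interruption optional, then resume at the same level |
| On treatment, grade 3 | Table 2, non-haematological | Hold (first mandatory action) |
| Start of a later cycle | Table 2 footnote | Blood counts only; no renal or bilirubin condition |

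For comparison, the irinotecan table in 6.2 requires a 25 mg/m² reduction already at grade 2.

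**2. Size of the day-8 step**

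2500 / 1500 = 1.67, an increase of 67%.

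**3. Scheduled checks to week 12**

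With 21-day cycles, biochemistry falls on days 1, 8, 22, 43, 64 and 85. That is five checks after the first dose. The gaps are 7, 14, 21, 21 and 21 days, so after the day-8 increase the next required test is 14 days later. At none of the five does a value above the 4.1 limit but below grade 3 require a metformin change.

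**4. Do other provisions fill the gap?**

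- *Intolerance (6.2).* The reduction is mandatory in wording, but no laboratory value triggers it. Section 6.1 equates good tolerance with absence of grade 3-4 events.
- *Contrast-related interruption (synopsis, section 5, 6.1).* The synopsis ties it by name to lactic acidosis. It is triggered by an imaging examination, at the radiology team's discretion, and not by an abnormal value.
- *Concomitant disease (6.3) and the exclusion for uncontrolled serious conditions (4.2).* Neither sets a renal or bilirubin limit; section 6.3 rests on investigator opinion, and 4.2 governs entry.
- *Re-escalation (6.2, Dose Scale).* After a reduction, every effort is to be made to restore the dose after at least a month. One of its criteria accepts resolution to grade 2 or lower, so it could reverse a reduction while a value still exceeds the entry limit.

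**The case against.** The best defence is that the event is rare by the protocol's own account, biochemistry is checked every cycle, grade 3 toxicity requires a hold, and investigators can interrupt at grade 2 or treat an abnormal value as intolerance. Section 6.1 says only that the dose *may* be raised. All of this is true and limits the seriousness. It does not close the gap: the synopsis and 6.2 direct the increase, and no text gives the entry limits any role after the first dose.

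Three stronger readings are tempting and should not be drawn.

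- *Every response below grade 3 is left to the investigator.* It is not. Table 2 tells the investigator to keep the dose at grade 1; only the grade 2 interruption is worded as optional.
- *Creatinine alone is an unsafe entry criterion and a clearance floor is needed.* As an illustration, assume upper limits of normal of 1.2-1.3 mg/dL (men) and 1.0-1.1 mg/dL (women), ages 40-75 and weights 50-80 kg. At 1.5 times the limit, Cockcroft-Gault runs from (140 − 75) × 50 / (72 × 1.5 × 1.3) = 23 mL/min (man, 75 years, 50 kg) to (140 − 40) × 80 × 0.85 / (72 × 1.5 × 1.0) = 63 mL/min (woman, 40 years, 80 kg). That shows one cut-off admits varied renal function. The protocol gives no clearance threshold and does not list the contraindications it mentions, so it cannot show that any of these values is unsafe or what the floor should be.
- *Many patients are exposed.* The documents give neither the grade cut-offs nor the number of patients near the limits. Five checks are five opportunities, not a measure of risk.

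**Conclusion.** The point holds as a gap in the on-treatment dosing rules. The renal and bilirubin limits bind only before the first dose. Afterwards the first mandatory metformin hold for non-haematological toxicity is at grade 3, and a patient above an entry limit but below grade 3 on day 8 can be escalated by 67%.

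This assumes that the CTCAE version 4 grade 3 threshold lies above the 1.5-times entry limit, for creatinine or for bilirubin. The protocol does not reproduce the cut-offs, so the sponsor should confirm this; the width of the gap and the number of the 41 planned patients it would touch remain unknown. The change is worth making because it applies the protocol's own safety condition with its own limits and tests. It does not bear on the validity of the primary efficacy analysis.

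**What to change.** **Synopsis, 6.1 and 6.2, day 8.** Require the 4.1 creatinine and bilirubin limits to be met on cycle 1 day 8 before escalation to 2500 mg/day; otherwise stay at 1500 mg/day. Use the same verb in all three places.

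**6.2, day 1 of each later cycle.** If either limit is exceeded below grade 3, reduce metformin by one level of Table 1. Hold it if the patient is already at 1000 mg/day or the value is worsening. Section 6.2 now allows the step from 1500 to 1000 mg/day for grade 3-4 toxicity, so that sentence needs widening, and the Table 2 grade 1 and 2 cells need a cross-reference.

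**Keep.** The grade 2 option to interrupt, the grade 3-4 rules, and the 3-week and 28-day stopping rules stay as they are. Exempting these holds from the stopping rules is not advised: it would permit open-ended irinotecan without metformin.

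**Dose Scale.** State that re-escalation applies only once the 4.1 limits are met again.

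**Cost.** Amendment wording only; no new visit, sample or test. Some patients will receive less metformin, which slightly lowers exposure to the drug under test, and a prolonged hold could end study treatment under the existing stopping rules.
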